**Fig. 1 Fig1:**
[figure not shown]
Telerehabilitation in a participant’s home

The exercise intervention consists of an individualised training programme of regular exercise of continuous or interval training on the treadmill and strength training exercises according to current guidelines [13]. The treadmill exercise programme lasts for at least 30 min. Depending on the patient’s condition, a programme of continuous training (moderate intensity - Borg scale [34] ratings up to 4) or interval training (high intensity - Borg scale ratings up to 6) is conducted. The frequency prescribed is 3–5 times/week for continuous training and 3 times/week for interval training. For interval training, up to 4 interval bouts of high intensity lasting from 1 to 4 min could be prescribed. Progression is made by increasing speed and incline first. Then the patient is encouraged to increase duration. Patients are permitted to take short rests if intolerable symptoms occur, but rest time does not count towards training duration. The exercise programme can be modified by the physiotherapist or the patients themselves according to their conditions. Strength training is prescribed for a frequency of 2–3 sessions per week. Each session includes at least two lower limb exercises (6–12 repetitions, 3 sets) and two upper limb exercises (6–12 repetitions, 1–3 sets). The patients can choose between sit-to-stand, squat, step-up, lunge, calf raise, biceps curl, shoulder press, wall push up, bench press, standing row, seated row, lateral pull down, triceps press. Bottles filled with sand/water or elastic bands/free weights can be used for upper limb exercises if already available in the patient’s home.

A customised website is used to access the individual training programme, fill in a daily diary and a training diary, review historical data, exchange electronic messages, schedule videoconferencing sessions, and assess individual goal settings and goal attainment. Patients are asked, every evening, to use their pulse oximeter at rest and to fill the daily electronic diary on the website including: a) oxygen saturation, b) heart rate, c) Breathlessness, Cough, and Sputum Scale (BCSS) [35], d) general wellbeing (qualitative self-score on a five-point Likert scale), and e) additional comments. During an exercise session on the treadmill, patients are required to self-monitor their oxygen saturation and heart rate. After each exercise session, patients are asked to fill in the electronic training diary on the website including: a) programme completion, b) Borg CR10 scale - Rating of Perceived Exertion for leg (highest value during exercise), c) Borg CR10 scale - Rating of Perceived Dyspnoea (highest value during exercise), d) oxygen saturation (lowest value during exercise), e) heart rate (highest value during exercise), and f) additional comments. The information sent through the electronic forms is monitored and interpreted weekly by a physiotherapist, who also checks for any out-of-range value. The physiotherapist can provide feedback to the patients via the website, or use this information in the upcoming videoconference. Patients are also informed on the presence of signs and symptoms to ensure that they do not exercise if not recommended.

Patients have scheduled videoconferencing sessions with the physiotherapist. During videoconferencing, patients are encouraged to set specific goals for their ongoing programme and their daily life activities. Self-management education and training are provided to promote adherence to health-enhancing behaviours. During disease exacerbations, strength training exercises might be encouraged until the patient gets well enough to exercise on the treadmill. If the patient reports changes on sputum aspect, guidance on airway clearance techniques is offered (e.g. active cycle of breathing). The physiotherapist can take electronic notes using the same website. The frequency of contacts consists of at least 1 individual videoconferencing session/week in the first 8 weeks after enrolment, and at least 1 individual videoconferencing session/month in the following period. Participants who experience a hospital admission during the study period are invited to continue their participation after discharge. In these cases, at least 1 individual videoconferencing session/week will be applied in the month after discharge as a reinforcement strategy. Additional peer-group exercise sessions supervised by the physiotherapist can be organised.

#### Treadmill arm

Patients in the treadmill arm are provided with a treadmill only to perform unsupervised exercise training at home. The exercise intervention consists of an individualised unsupervised training programme performed as prescribed to the participants in the telerehabilitation arm, without regular review or progression of the program. Participants are asked to record each training session on a paper-based diary. This intervention arm allows comparing the effects of providing training equipment only to those using telerehabilitation.

#### Control arm

Patients in the control arm are offered standard care. To ensure that no participants are denied access to the best health care practice, any participant in the trial can undertake a traditional PR programme at any time during the 2-year study period if it is considered clinically indicated by their usual treating team.

### Recruitment and study procedures

At enrolment, a clinical assessment is performed for all the patients by appropriately trained study personnel blinded to group allocation. Participants are asked to perform spirometry, the 6-min walking test [36] and complete the study questionnaires (Table 1). Participants are also provided brochures containing information about PR, physical activity and training, diet, self-management, motivation and lifestyle changes, smoking cessation and oxygen therapy.

**Table 1 Tab1:** Data collected at baseline and follow-up visits

Data collected	Baseline	6-month	1-year	2-year
Clinical history and patient’s characteristics	X			
Pharmacological treatment	X			
Spirometry	X	X	X	X
6-min walking test	X	X	X	X
MMRC Dyspnoea Scale	X	X	X	X
COPD Assessment Test	X	X	X	X
EQ-5D Health Questionnaire	X	X	X	X
Generalised Self-Efficacy Scale	X	X	X	X
Hospital Anxiety and Depression Scale	X	X	X	X
Level of physical activity	X	X	X	X
Healthcare utilisation		X	X	X
Patient Global Impression of Change		X		

After enrolment, patients in the telerehabilitation and the treadmill arms undergo a supervised session on the treadmill with an experienced research physiotherapist to learn how to safely exercise at home, receive information on how to make progress in the programme and are given the opportunity to clarify any questions related to equipment management. Patients in the telerehabilitation arm also receive training on the use of the study website. A test videoconferencing session is also performed by the local research team to guarantee proper equipment functioning. Patients can always contact the research team in case of technical issues.

At 6-month, 1-year and 2-year, patients undergo a clinical reassessment and are asked to complete the study questionnaires (Table 1). During data collection patients are encouraged to continue participating in the study. Patients are discharged from the trial after 2 years, those in the telerehabilitation and the treadmill arms can keep the equipment at the end of the study.

### Outcome measures

The primary outcome is the combined number of hospitalisations and ED presentations. Differences in the rate of events between the study arms will be measured at all assessment time points (Table 2). Data on hospitalisations and ED presentations, together with outpatient visits, will be collected from hospitals records (in Australia), regional systems (in Denmark) and national registries (in Norway). Details will include institution, date of admission, date of discharge, diagnosis-related group (DRG), diagnoses, procedures and associated cost. In addition, use of hospital resources will be recorded during the follow-up visits. Hospitalisations and ED presentations will be also analysed separately as secondary outcomes. Mortality will be monitored along the study together with dropouts.

**Table 2 Tab2:** Primary and secondary outcomes and related measures

Outcome	Measure
Primary outcome	
• Combined number of hospitalisations and ED presentations	• Incidence Density
Secondary outcomes	
• Hospitalisations • ED presentations • Mortality • Time free from first event • Health status • Quality of life • Anxiety and depression • Self-efficacy • Subjective impression of overall change • Physical performance • Level of physical activity	• Incidence Density • Incidence Density • Mortality rate • Days to first hospitalisation or ED presentation • COPD Assessment Test • EQ-5D • Hospital Anxiety and Depression Scale (HAD) • Generalised Self-Efficacy Scale (GSES) • Patient global impression of change scale (PGIC) • 6-min walking distance (6MWD) • Daily number of steps, minutes of moderate to vigorous physical activity and sedentary time during 1-week
• Cost-effectiveness • Experiences in telerehabilitation	• Cost-utility analysis (cost-per-QALY) • Qualitative interviews with semi-structured questions

Health status will be measured with the COPD Assessment Test (CAT) [37]. Health-related quality of life will be measured with the EQ-5D questionnaire [38]. Levels of anxiety and depression will be measured with the Hospital Anxiety and Depression Scale (HAD) [39]. Self-efficacy will be measured with the Generalised Self-Efficacy Scale (GSES) [40]. Subjective impression of overall change will be measured with the Patient global impression of change scale (PGIC) [41]. The study questionnaires, available in English, Norwegian and Danish with validated versions, will be collected along the study at different time points (Table 1).

Functional exercise capacity will be measured with the 6-min walking distance (6MWD). The 6-min walking test will be performed twice according to guidelines, and the furthest distance recorded [36].

Objective physical activity assessment will be undertaken using the SenseWear Armband (SWA; BodyMedia, Pittsburgh, USA; professional software version 7.0). The SWA will be positioned on the participant’s left upper arm according to manufacturer instructions. Participants will be instructed to wear the SWA for 1 week, only removing it for bathing or water-based activities. The first and last days of data will be excluded from analysis upon data retrieval. A day of data (midnight to 23:59) will be included for analysis if there is at least 10 h of data within the 24-h period. A minimum of four valid days of data will be required per participant at each assessment time point [42], inclusive of at least 1 weekend day. The proprietary algorithm provides a range of variables for each minute of wear time, including energy expenditure and number of steps. The intensity of physical activity is described according to metabolic equivalents (1 MET = 1 kcal/kg/h). Each minute of wear time will be allocated to a category of physical activity on the basis of MET classification (sedentary ≤ 1.5 METs, moderate and vigorous ≥ 3 METs). The amount of time spent in moderate to vigorous physical activity, and time spent sedentary, will be calculated.

A cost-utility analysis will be performed to verify whether the telerehabilitation and the treadmill interventions are cost-effective. The perspective of the healthcare authority will be adopted with respect to costs. The following cost components will be included in the analysis: a) hospital resources, b) delivery of the telerehabilitation intervention, and c) equipment. Hospital resources will include hospitalisations, ED presentations, outpatient visits, and rehabilitation. Unit cost for each resource will be based on the specific public tariffs from the national DRG system. Delivery of the telerehabilitation intervention will include the time used by the project team to install the equipment in the patient’s home and provide training, and the time used by the physiotherapist to supervise the patients. Equipment costs for the telerehabilitation arm and the intervention arm will be calculated based on a 5-year amortisation period. All costs will be expressed in Euros (€). Utility will be measured in terms of quality adjusted life years (QALYs), based on the answers of the EQ-5D questionnaires at baseline, 6 month, 1–2 years. Utility values will be calculated using the European EQ-net VAS set, and only if all the five dimensions are answered. The incremental cost-effectiveness ratio will be computed as differential costs and differential QALYs.

Patients’ perspectives in participating in long-term telerehabilitation will be explored through qualitative interviews with semi-structured questions. Interviews will be conducted before telerehabilitation, after 1 year and after 2 years, with 5–8 patients in the telerehabilitation arm at each site. Interviews will be recorded on audio digital file, transcribed verbatim and analysed via Nvivo 10.0 upon the theoretical frame of the learning theory [43].

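### As written, sedentary time counts sleep, and it can be dominated by armband wear time if night wear varies between participants or visits

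*Protocol article*

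**What the plan says.** The physical activity paragraph of the Protocol article, Outcome measures, fixes four things.

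- **Wear.** "Participants will be instructed to wear the SWA for 1 week, only removing it for bathing or water-based activities". Nights are therefore included.
- **Valid day.** A calendar day "will be included for analysis if there is at least 10 h of data within the 24-h period". The first and last days are dropped. "A minimum of four valid days of data will be required per participant at each assessment time point", at least one of them at a weekend.
- **Classification.** "Each minute of wear time will be allocated to a category of physical activity on the basis of MET classification", with the cut-offs "sedentary ≤ 1.5 METs, moderate and vigorous ≥ 3 METs". Intensity is the only criterion.
- **Summary.** The sedentary result is an amount of time. No waking condition and no scaling to wear time is stated.

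Table 2 lists "minutes of moderate to vigorous physical activity and sedentary time during 1-week", together with daily steps, as the measures of the secondary outcome on level of physical activity. Table 1 schedules the assessment at baseline, 6 months, 1 year and 2 years. The Statistical analysis section analyses change from baseline with linear mixed models.

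**The concern.** Under this rule a minute asleep counts the same as a minute sitting awake. The 10-hour threshold does not prevent this, because it asks for hours of data and not waking hours: eight hours asleep from midnight plus two more hours already make a valid day.

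The quantity is also absolute, while valid days may hold anything from 10 to 24 h of data. A participant who wears the band overnight at one visit and removes it at night at another shows a change of about one night's sleep with no change in behaviour.

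Improved physical activity is part of the trial's hypothesis (Background), so a noisy measure of it has a cost. Participants know which arm they are in, so wear habits could in principle diverge between arms and bias the comparison.

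**Working it through.** The document gives no figure for sedentary or wear time, so there is nothing to reproduce. The inputs taken from it are the 1.5 MET cut-off, the wear instruction and the 10-hour rule. All behavioural values below are assumptions. Sleep is taken to fall at or below 1.5 METs because it is a resting state and the protocol sets 1 MET at 1 kcal/kg/h.

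**Step 1: counted sedentary time for one fixed behaviour.** Let f be the sedentary share of waking time, W the waking hours worn and N the sleeping hours worn. Counted sedentary time is S = f × W + N. With 8 h of sleep and f = 0.65:

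| Valid day | Calculation | S |
|---|---|---|
| 24 h wear | 0.65 × 16 + 8 | 18.4 h |
| 16 h, waking only | 0.65 × 16 | 10.4 h |
| 10 h, waking only | 0.65 × 10 | 6.5 h |
| 10 h, of which 8 asleep | 0.65 × 2 + 8 | 9.3 h |

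With sleep of 7-9 h and f of 0.55-0.75, full wear gives 0.55 × 17 + 7 = 16.35 h up to 0.75 × 15 + 9 = 20.25 h. Ten waking hours give 5.5 to 7.5 h.

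**Step 2: share of sleep on a full-wear day.** The share is N / S. Lowest: 7 / (0.75 × 17 + 7) = 7 / 19.75 = 35%. Highest: 9 / (0.55 × 15 + 9) = 9 / 17.25 = 52%.

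**Step 3: how far wear time drives differences between participants.** This is a simulation of 200,000 participants at a single visit. Sleep has mean 8 h and SD 1 h. f has mean 0.65 and between-person SD of 5, 10 or 15 percentage points. Waking removal averages under 1 h. The share wearing the band at night is varied. R-squared of counted sedentary time with wear time:

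| Wear at night | SD 5 | SD 10 | SD 15 |
|---|---|---|---|
| 100% | 0.14 | 0.05 | 0.02 |
| 95% | 0.81 | 0.55 | 0.37 |
| 90% | 0.89 | 0.70 | 0.53 |
| 80% | 0.93 | 0.81 | 0.67 |
| 50% | 0.96 | 0.87 | 0.76 |

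R-squared with true waking sedentary time is 0.64 at 100% night wear (0.17 to 0.81 across the three SDs). At SD 10 it falls to 0.30 at 95% and 0.21 at 90%. If no sleep is counted it is about 0.96 (SD 10). That last figure is for waking sedentary minutes and assumes sleep is identified without error.

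**Step 4: what a shift in one arm would do.** There are 40 patients per arm (Sample size). Suppose that at a follow-up visit four more participants in one arm wear the band at night, with no such difference at baseline. The arm mean moves by 4/40 × 7-9 h = 0.7-0.9 h, or 42-54 min per day, with no difference in behaviour. This is an illustration; nothing in the document predicts it.

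**The case against.** The best defence is that the rule works tolerably if the wear instruction is followed. Wear then hardly varies and explains only about 2-14% of the variance. On a complete 24-hour day, counted sedentary time equals 24 h minus non-sedentary waking time, so it still carries information on inactivity. In the simulation its R-squared with the waking sedentary share is 0.90 (0.71 to 0.95). A reader might infer that the outcome mostly reflects how long the band was worn, or does not measure inactivity at all. Neither follows, because both depend on compliance, which the document does not report.

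The design also limits the damage. A stable habit of night wear or removal largely cancels in change from baseline. The first and last days are dropped and at least four valid days are needed. All arms receive the same instruction, so a difference in wear between arms is conjecture.

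Two further readings are tempting. One takes the span of valid wear, (24 − 10) × 60 = 840 min, as the likely error. It is a ceiling on recorded time between two extreme single days; even the extremes in Step 1 differ by 18.4 − 6.5 = 11.9 h of sedentary time. The other extends the point to steps and active minutes. Those do not count sleep, and little is lost from them if the band comes off only at night.

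Finally, sleep scoring and wear-time adjustment are often left to an SAP, and none is shown. That holds for the adjustment. It does not hold for sleep: the article itself fixes the unit classified, the cut-offs and the valid-day rule, and an SAP that removed sleep would have to change them.

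**Conclusion.** The point holds in a limited form. The stated rule counts sleep as sedentary, at about 35-52% of the total on a full-wear day under the assumed sleep and sedentary ranges. It also makes the total depend on hours worn: 18.4, 10.4 or 6.5 h for the same assumed behaviour, all on valid days.

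Wear time becomes the main source of variation between participants once roughly 5-10% of them remove the band at night, or fewer if true behaviour varies little. With full compliance it does not, and the remaining problem is dilution by sleep.

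The expected consequence is noise in one of three measures of one secondary outcome. Bias would need night wear to change differently by arm, on which the document gives no data. The primary outcome, the sample size and the cost-utility analysis are untouched. The correction is still worth making, because it is inexpensive and the present rule is explicit.

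**What to change.** Restrict sedentary minutes, and the 10-hour validity rule, to waking wear. Identify sleep from the device's own output if that is available; the article does not mention one. Otherwise exclude a fixed night window, applied identically to all arms and visits. Report sedentary time as a proportion of waking wear time.

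Wear time is measured after randomisation and might itself be affected by arm, so a model with a wear-time covariate should be a sensitivity analysis only.

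The device gives values for each minute worn, so this is a reprocessing rule for recorded data and needs no new measurement. It should be fixed before the data are compared by arm. The costs are that some participant-visits may fall below 10 waking hours and be excluded, in a number the document does not allow one to estimate, and that a fixed night window will misclassify some minutes for people with unusual sleep hours.

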### Adverse events and dropouts

Adverse events, including deaths, treadmill injuries and other unspecified reasons, will be recorded in the WebCRF program. Technical problems will be recorded by each participating centre into a separate database. Dropouts will occur if patients notify the research team that they do not want to participate any longer to the study and therefore withdraw their consent. In this case the project team might collect the equipment upon request. Patients who do not participate actively in the intervention will still be included in the study, and analysed according to the intention-to-treat approach. They will keep the project equipment as long as they want.

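### The cost-utility analysis costs staff delivery time for telerehabilitation only, so the treadmill arm's share of set-up and training cost is left out

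*Protocol article*

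**What the plan says.** The cost-utility paragraph under Outcome measures takes the healthcare authority's perspective and asks whether each of the two home-exercise interventions is cost-effective. It names three cost components. The first is hospital resources; the other two are "b) delivery of the telerehabilitation intervention, and c) equipment". The delivery component is then spelled out as project-team time for home installation and training, plus physiotherapist time for supervision. All of it sits under the telerehabilitation label.

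On equipment it says "Equipment costs for the telerehabilitation arm and the intervention arm will be calculated based on a 5-year amortisation period". The second label in that sentence most plausibly means the treadmill arm, because the section Treadmill arm uses the same term for it.

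Two other sections bear on this. Treadmill arm says that these patients are given a treadmill for use at home. Recruitment and study procedures says that "patients in the telerehabilitation and the treadmill arms undergo a supervised session on the treadmill with an experienced research physiotherapist". The same section says that "Patients are discharged from the trial after 2 years" and that "those in the telerehabilitation and the treadmill arms can keep the equipment at the end of the study".

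**The concern.** Installing a treadmill and teaching the patient to use it safely takes staff time in both equipment arms. If only one arm is charged for it, the error is not random. It makes treadmill training look cheaper against standard care than it is, and it makes telemonitoring look dearer than it is.

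The second effect goes to the purpose of the design. The Discussion gives the reason for three arms as separating the effect of home equipment from that of telemonitoring. The telerehabilitation versus treadmill contrast should therefore price what telemonitoring adds. As written, it also carries set-up work that both arms need.

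Cost-effectiveness is a secondary outcome, but it is the conclusion that the abstract and the Discussion promise to decision makers.

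A related question concerns equipment. Cost is spread over 5 years, follow-up ends at 2, and patients may keep what they were given. The article states neither a horizon for the cost analysis nor what happens to the unamortised value.

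**Working it through.** The article states no cost, staff time or cost-effectiveness ratio, so there is no figure of its own to reproduce. The check is algebraic.

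**Inputs**
- Arms evaluated, cost components and 5-year amortisation: Outcome measures.
- Treadmill only in the treadmill arm: Treadmill arm. Treadmill, pulse oximeter, tablet and holder in the telerehabilitation arm: Telerehabilitation arm.
- Supervised treadmill session in both equipment arms; extra website training and a test videoconference in the telerehabilitation arm only: Recruitment and study procedures.
- Utilities "based on the answers of the EQ-5D questionnaires at baseline", 6 months, 1 year and 2 years: Outcome measures.

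**Notation, per patient**
- T = treadmill price; K = price of tablet, oximeter and holder.
- D = installation, training and supervised-session time that both equipment arms need.
- S = all other telerehabilitation delivery time (website training, test call, ongoing supervision).
- a = share of the equipment price charged within the analysis horizon.

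Hospital costs are left out because the rule in question does not touch them. T and D are taken as equal in the two equipment arms.

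**Step 1: the delivery component**

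| Contrast | Incremental cost as written | With D charged in both arms | Change |
|---|---|---|---|
| Telerehabilitation − control | a(T+K) + D + S | a(T+K) + D + S | 0 |
| Treadmill − control | aT | aT + D | +D |
| Telerehabilitation − treadmill | aK + D + S | aK + S | −D |

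For a QALY difference ΔE in the relevant contrast, the ratio shifts by D/ΔE for treadmill versus control and by −D/ΔE for telerehabilitation versus treadmill. Neither D nor ΔE is given, so no ratio can be computed. With 120/3 = 40 patients in the treadmill arm, the omitted total is 40 × D.

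**Step 2: the equipment share**

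If the horizon equals the 2-year follow-up and the write-off is straight-line, a = 2/5 = 40 %, leaving 60 % uncharged. With an equivalent annual cost, the present-value share is A(2)/A(5), where A(n) = (1 − (1+r)^−n)/r. At assumed discount rates:
- r = 3 %: 1.913/4.580 = 42 %; as an undiscounted sum, 2/4.580 = 44 %.
- r = 5 %: 1.859/4.329 = 43 %; as an undiscounted sum, 2/4.329 = 46 %.

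So a lies between 40 % and 46 % under these assumptions. The article itself states none of these shares.

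**Step 3: what a full-price sensitivity analysis would change**

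Moving from a = 0.4 to a = 1, with D charged in both arms, changes the as-written incremental costs as follows:
- Telerehabilitation − control: +0.6(T+K).
- Treadmill − control: +0.6T + D.
- Telerehabilitation − treadmill: +0.6K − D.

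In the last line T cancels if the two arms use the same model within a country. The two changes then oppose each other, and the sign turns at D = 0.6K.

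**The case against.** **The delivery wording may be shorthand.** No sentence sets the treadmill arm's delivery cost to zero, and the amount is probably small: one installation and one session. That limits the size of the point but does not remove it. The equipment sentence in the same paragraph names a second arm and the delivery component does not, so an analyst following the text would cost staff time in one arm only.

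**Amortisation over useful life is accepted practice.** A reader might infer that 60 % of the equipment cost is wrongly omitted and that full price should be the base case. The document does not support that. Spreading the price matches about 2 years of cost to 2 years of QALYs, whereas charging all of it against 2 years of benefit would ignore later use of equipment that patients still have. Some of it is also recoverable: for patients who withdraw, "In this case the project team might collect the equipment upon request". What stands on the other side is that a payer who gives the equipment away does not get the remainder back. This is a contestable choice, and it justifies a sensitivity analysis but not a change of base case.

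**Deaths.** A reader might infer that patients who die drop out of the QALYs, because utilities are computed "only if all the five dimensions are answered". That is a scoring rule for incomplete questionnaires. The article says nothing about excluding deaths, it monitors mortality, and Statistical analysis specifies intention-to-treat on all randomised patients. How death enters the QALYs is a detail that an article can leave to the full plan.

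**Conclusion.** The concern holds for the delivery cost. As written, incremental cost is understated by D for treadmill versus control and overstated by D for telerehabilitation versus treadmill. D is the set-up and training cost that both equipment arms share, and it is taken as equal in the two arms. The direction follows from the text; the size cannot be obtained from it and is probably modest.

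A reader might infer that all the cost-effectiveness ratios are biased. They are not: the delivery gap touches two of three contrasts, and telerehabilitation versus control is unaffected. The equipment rule would reach all three only if full-price charging were accepted as the correct standard, which has not been shown. No amount in euros can be attached to either issue, because the article gives no prices.

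The primary outcome and its analysis are untouched.

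**What to change.** - Reword component b) so that it covers delivery of the telerehabilitation and treadmill interventions. Log and cost installation, training and the supervised session in both equipment arms, and keep ongoing physiotherapist supervision as a telerehabilitation cost.
- Name the treadmill arm explicitly in the equipment sentence, and state the horizon of the cost-utility analysis.
- Keep 5-year amortisation as the base case, and add a sensitivity analysis that charges the full purchase price of equipment left with the patient.

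The cost is a little staff-time logging and a less favourable treadmill versus control ratio. Trial status reports that recruitment is continuing, so time can be logged prospectively for new patients; for installations already done it would have to be estimated. The sensitivity analysis needs only purchase prices.

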## Methods/Design

### Design

An international multicentre randomised controlled trial (RCT) conducted across sites in three countries (Norway, Australia, and Denmark), where 120 patients with COPD are randomly assigned to three arms (telerehabilitation, treadmill, control) in a 1:1:1 ratio and followed up for 2 years. The trial is restricted to patients who have volunteered and provided written informed consent in accordance with the Declaration of Helsinki. The trial received approval from the Regional Committee for Medical and Health Research Ethics in Norway (2014/676/REK nord), the Alfred Hospital Human Research Ethics Committee (289/14), and the North Denmark Region Committee on Health Research Ethics (N-20140038). The protocol of this RCT fulfils the Standard Protocol Items: Recommendations for Interventional Trials (SPIRIT) guidelines (Additional file 1).

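### The cost-per-QALY result rests only on a rating-scale (VAS) value set, so it is not directly comparable with ratios built on choice-based utilities

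*Protocol article*

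**What the plan says.** Table 2 of the protocol article lists cost-effectiveness among the secondary outcomes, measured as cost per QALY. Outcome measures gives the purpose: "A cost-utility analysis will be performed to verify whether the telerehabilitation and the treadmill interventions are cost-effective". The effect side is described as follows: "Utility will be measured in terms of quality adjusted life years (QALYs), based on the answers of the EQ-5D questionnaires", with answers taken at baseline, 6 months, 1 year and 2 years. The scoring rule is "Utility values will be calculated using the European EQ-net VAS set", restricted to questionnaires with no dimension left blank. The decision statistic is then given: "The incremental cost-effectiveness ratio will be computed as differential costs and differential QALYs". On the cost side, "Unit cost for each resource will be based on the specific public tariffs from the national DRG system", with all costs expressed in Euros.

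The European VAS set is the only value set named, and it applies to all patients in Norway, Australia and Denmark. No willingness-to-pay threshold is stated. The Discussion paragraph of the Abstract and the main Discussion both say that the trial will show whether long-term telerehabilitation is a cost-effective strategy. The Background says that the results are meant for decision makers as well as practitioners.

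**The concern.** A QALY multiplies time by a weight. For the product to mean anything as an exchange of quality for quantity of life, the weight has to say how much life would be given up for better health. A time trade-off set is built on that question. A VAS set is built by asking people to place health states on a visual scale, and nothing is given up in doing so. The article nevertheless calls the VAS values utilities and uses them as QALY weights.

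The two kinds of set can space the same EQ-5D states differently, so the same patients' answers can give different QALY differences and different ratios. Because the article states no threshold, a reader who wants to know whether the programme is cost-effective has to set its ratio beside other cost-per-QALY figures. Where those rest on choice-based weights, the comparison mixes two scales, and a decision maker could be led to accept or reject the programme partly because of the scoring set.

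**Working it through.** **What can be reproduced.** The article states no utility, QALY difference, cost difference or ratio, so there is no planned economic figure to reproduce. Its planning figure of 65 person-years per group belongs to the primary outcome and does not enter here.

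**Inputs from the article (Outcome measures).** The value set is the European VAS set, the outcome is QALYs from EQ-5D, and the statistic is the incremental cost-effectiveness ratio (ICER). Every other number below is an assumption for illustration.

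**Step 1: how the ratio depends on the set.**

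ICER = ΔC / ΔQ, where ΔC is the cost difference and ΔQ the QALY difference.

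The value set does not touch ΔC. If moving from the VAS set to a choice-based set multiplies ΔQ by k, then

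ICER(choice-based) = ΔC / (k × ΔQ) = ICER(VAS) × 1/k.

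| Assumed k | Multiplier of the ICER, 1/k |
|---|---|
| 0.6 | 1.67 |
| 0.7 | 1.43 |
| 0.8 | 1.25 |
| 1.0 | 1.00 |
| 1.25 | 0.80 |
| 1.5 | 0.67 |

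**Step 2: in money, with assumed figures.** Take ΔC = EUR 3,000 and ΔQ = 0.080 on the VAS set.

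- VAS set: 3,000 / 0.080 = EUR 37,500 per QALY.
- k = 0.6: ΔQ = 0.048, and 3,000 / 0.048 = EUR 62,500 per QALY.
- k = 1.5: ΔQ = 0.120, and 3,000 / 0.120 = EUR 25,000 per QALY.

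The same trial data give a higher or a lower ratio according to k, and the documents do not say on which side of 1 it lies.

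**Step 3: is the difference always a plain rescaling?** With one constant positive k, the sign of ΔQ cannot change. An arm that costs less and gains QALYs remains dominant. But two sets need not be constant multiples of each other, and deaths bring in the level of the weight as well as differences between weights. A hypothetical case: one arm loses 0.03 life-years at weight 0.60 and gains 0.01 in weight over 2 years.

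- First set: 2 × 0.01 − 0.03 × 0.60 = 0.020 − 0.018 = +0.002 QALY.
- Second set, with distances from full health 30 % shorter: the weight is 1 − 0.7 × 0.40 = 0.72 and the gain is 0.7 × 0.01 = 0.007. Then 2 × 0.007 − 0.03 × 0.72 = 0.014 − 0.0216 = −0.0076 QALY.

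The sign changes. The net gain in this example is close to zero by construction. It shows only that a change of set is not guaranteed to be a harmless rescaling, and it predicts nothing about this trial.

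**The case against.** **The result may not depend on the set.** The trial hypothesises fewer readmissions, so hospital costs could fall. If an arm were cheaper and gained QALYs, a constant rescaling would leave it dominant. This stands for that scenario, subject to step 3. A reader might infer that the VAS set makes any cost-effectiveness conclusion impossible. The documents do not support that: they state no threshold against which the ratio would be misread, and a dominant result could survive.

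**The size is assumed.** This stands in full. A reader might also infer that the VAS set makes the programme look worse than it is, or better. Nothing in the article gives the direction.

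**One set for three countries is reasonable.** This stands too. It is tempting to fault a European set because Australian patients are scored with it, or because national tariffs are paired with a common valuation. Yet any single set will be foreign to some patients in a three-country trial, and a common set keeps pooled QALYs on one scale. The number of Australian patients is not given. The fix below also uses one common set.

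**The article is condensed.** Sensitivity analyses on the value set may be in a fuller document, and their absence here is not a fault. The named set, however, is a stated choice rather than an omitted detail, and that choice is the point.

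**No decision-maker requirement is cited.** This is correct. The case for a choice-based set rests on what a QALY weight has to measure and on the comparison that readers will need to make.

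**Conclusion.** The point holds as a minor one. The weights named for the cost-per-QALY analysis are ratings, and calling them utilities does not make them choice-based. A ratio resting on them alone is not directly comparable with ratios from choice-based weights, and so cannot by itself carry the cost-effectiveness conclusion that the article promises.

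The effect on the ratio is a factor of 1/k, which is 1.67 to 0.67 for an assumed k of 0.6 to 1.5. That range is an assumption and treats k as constant. The true size and direction cannot be derived from the documents. The point concerns one secondary economic outcome. The primary outcome, the sample size and the clinical comparisons are untouched.

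**What to change.** Before results are seen, name one published choice-based (time trade-off) EQ-5D value set that matches the EQ-5D version used. Apply it to all patients as the base case, and report the European VAS set alongside as a sensitivity analysis. Analyses with country-specific sets are optional.

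The cost is a re-scoring of EQ-5D answers that are already planned at all four time points. No new patients, visits or questionnaires are needed. The downside is an extra result line and less comparability of the base case with earlier reports that used the VAS set; keeping that set as a sensitivity analysis preserves the link. Fixing the set in advance also removes any suspicion that it was chosen for its result.
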